## 4.5.2 Study Time Line

---

All follow-up windows are based on “Day 0” which for this study is the day of cervical spondylotic myelopathy surgery.

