#### 4.1.1 Primary Endpoint

---

- Absolute change in mJOA from admission to 180 days

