#### *4.5.2.4 Visit 3: Admission (pre-surgery)*

---

This visit occurs when the patient is admitted to the hospital for surgery. During the hospital stay the subject should receive scheduled study medication. Study coordinator should coordinate with the hospital pharmacy to assure that the subject receives the study medication during the hospital stay.

The following activities should be performed at admission:

- Record date and time of hospital admission
- Check and record AEs/SAEs
- Check and record concomitant therapy
- Obtain and record vital signs
- Obtain blood sample and order clinical lab tests
- Collect the medications and the Bottle #1 dispensed at enrollment visit.
- Count and record the remaining medication. The remaining medication and its container will be counted and compared with the data from Subject's Medication Compliance Diary. Record study medication compliance on the Medication Compliance CRF.
- Ensure the subject receives study medication during the hospital stay, and record in the Subject's Medication Compliance Diary. Bottle #2 should be dispensed on the surgery day (Day 0)
- Log the subject's drug accountability information into the Site Drug Accountability Log
- Investigator:
  - Obtain and record mJOA, Nurick, Grip Strength
  - Perform and record ASIA (complete)
- Subject:
  - Fill-out entire Subject pre-surgical source worksheet with data on health behavior, NDI, SF36v2.0, EQ-5D, Pain NRS, Bazaz
- Check source worksheets for completeness
- Verify data and enter into eCRF within 14 calendar days of collection

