### 4.5.3 Enrollment and Randomization

---

Patient enrollment occurs at the time of randomization. If a patient is consented, screened, and, for any reason, does not get randomized, the patient will not be considered enrolled into the study.

Patient randomization occurs at Visit 2 (Enrollment), 15-21 days prior to the surgery. The randomization will occur by opening the lowest sequential number of the sealed randomization envelopes. Inside the envelope there will be a unique patient randomization number. The study coordinator will match the unique patient randomization number with the number on the medication container. The randomization will be recorded in the Randomization Log.

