##### 4.6.2 Enrolled Subject

A subject is considered to be enrolled when the randomization occurs.

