### 5.10.1 Intention-to-Treat

---

Consenting patients who qualify and are randomized to a study arm (i.e. enrolled subjects) will be included in the Intent-To-Treat (ITT) analytic sample primary analysis population, regardless of the actual treatment received. Screen failures will be recorded on a screening eCRF and will not be included in the ITT group. Values for the patients who do not have the 6-month end point will be imputed to create complete ITT population.

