### 5.10.3 Per-protocol Population

---

Enrolled subjects who receive at least 80% of the treatment medication (riluzole or placebo) and receive the surgery will form per-protocol population.

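### A randomised subject who is never operated on has no defined 180-day visit, so the ITT analysis imputes a primary outcome that could have been measured

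*Protocol*

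**What the plan says.** **Clock.** Protocol 4.5.2: "All follow-up windows are based on" Day 0, "which for this study is the day of cervical spondylotic myelopathy surgery". Table 1 and sections 4.5.2.7 to 4.5.2.9 give the 35-, 180- and 365-day visits no other anchor.

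**Entry.** Section 4.5.3: "Patient randomization occurs at Visit 2 (Enrollment), 15-21 days prior to the surgery". Section 4.6.2: "A subject is considered to be enrolled when the randomization occurs". The trial clock therefore starts after the subject is already in the trial.

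**Start of the primary endpoint.** Section 4.1.1: "Absolute change in mJOA from admission to 180 days". Section 4.5.2.4 says of the admission visit: "This visit occurs when the patient is admitted to the hospital for surgery".

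**Analysis.** Section 5.10.1 keeps every randomised subject in the ITT set whatever treatment followed, and adds: "Values for the patients who do not have the 6-month end point will be imputed to create complete ITT population". Section 5.10.5 makes ITT the primary efficacy population.

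**Non-operated subjects are foreseen.** Section 5.10.3 builds the per-protocol set from "Enrolled subjects who receive at least 80% of the treatment medication (riluzole or placebo) and receive the surgery". The surgery condition would be idle if every enrolled subject were operated on.

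**The concern.** The protocol retains a non-operated subject in the primary analysis but sets no time at which to measure the primary outcome. Keeping all randomised subjects protects the comparison only if their outcomes are also sought. Here a site that follows the visit schedule as written has no 180-day visit to hold, and the analysis fills the gap by imputation.

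Two things are at stake. First, the data loss is avoidable and permanent: an SAP can choose how to impute, but it cannot recover an assessment that the protocol did not schedule. Second, surgery may be cancelled after as much as two weeks on study drug, so the share not operated on may differ by arm. If the imputed value came from operated subjects, it would credit a post-surgical gain to people who had no operation.

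**Working it through.** **Does another section close the gap?**
- Section 4.6.3 lists two reasons for withdrawal: the subject's own decision, and the investigator's decision for safety or non-compliance. Cancelled surgery is not listed, so such a subject has not left the study.
- Section 4.5.2.10 (unscheduled visit) has no time anchor, but records only concomitant therapy and adverse events, not mJOA.
- Section 4.5.1 rules out collecting data by phone or mail.
- Section 4.5.4.5 says that drug-non-compliant subjects stay and follow the same procedures. There is no matching rule for non-operated subjects.
- Section 4.6.5 also counts completion from surgery.

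None supplies a 180-day mJOA. A subject cancelled before admission also lacks the starting value in 4.1.1 and has only the enrollment or screening mJOA (4.5.2.2, 4.5.2.3).

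**The plan's own figures.** Inputs from 5.7 and Table 3: difference 0.9, SD 2.57, one-sided alpha 0.025, power 0.80, looks at 65% and 100%.
- Fixed design: 129 per arm.
- Two looks, Lan-DeMets O'Brien-Fleming alpha spending, gamma(-2) non-binding futility: efficacy bounds z = 2.547 and 1.990, futility bound 0.938. Table 4 has 2.5469, 1.9896 and 0.9365.
- Power at N = 270: 41.0% at the interim and 80.05% overall. Section 5.8 has 40.95% and 80.05%.
- Enrolled: 270 / (1 − 0.10) = 300.

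The sample size reproduces. The gap lies in the visit schedule.

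**Number affected.** The protocol gives no cancellation rate q, so 1-5% is an assumption.
- q = 1%: 0.01 × 300 = 3
- q = 2%: 0.02 × 300 = 6
- q = 5%: 0.05 × 300 = 15

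**Power if imputed subjects add no information**, with 10% ordinary loss among the rest: measured N = 300 × (1 − q) × 0.9.
- q = 1%: 267, power 79.7%
- q = 2%: 265, power 79.3%
- q = 5%: 257, power 78.0%

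Measuring these subjects does not buy power. If they show no difference between arms, the expected difference is 0.9 × (1 − q); at N = 270 and SD 2.57, power is 79.3%, 78.4% and 75.9%. The reason to measure them is to have an observed ITT outcome.

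**Possible bias.** Let p_R and p_P be the non-operated shares on riluzole and placebo, m the value imputed in both arms, and d the true mean change without surgery.

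Bias in the difference = (p_R − p_P) × (m − d)

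Take d = 0 (assumption) and m = 2.81, the mean change in the sponsor's earlier CSM study (5.7).
- p_R = p_P: bias 0
- m = 0 (no change imputed): bias 0
- 2 points more on riluzole: 0.02 × 2.81 = 0.056, or 0.056 / 0.9 = 6% of the design effect
- 5 points more on riluzole: 0.05 × 2.81 = 0.141, or 0.141 / 0.9 = 16%
- 2 or 5 points more on placebo: −0.056 or −0.141

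A 5-point imbalance at 5% overall means 7.5% against 2.5%, a threefold ratio. For scale, the standard error of the difference at 135 per arm is 2.57 × √(2/135) = 0.31, so the largest value is under half of one standard error.

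**The case against.** Timing follow-up from the operation is an ordinary choice in a surgical trial, and 4.5.2 contains no error in itself. The protocol is silent on cancelled surgery: it neither ends follow-up nor forbids a visit, and it speaks of follow-up windows, not of every visit. That stands, and the point is limited to what the schedule leaves undefined.

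A reader might go further and infer that the ITT estimate will be biased in favour of riluzole. The document does not support that. Section 5.10.1 names no imputation method, and section 5 leaves analysis details to an SAP that is not at hand. An SAP that imputed no change for non-operated subjects would remove the bias calculated above. Nothing shows that cancellation would be more frequent on riluzole. It is also tempting to argue that abnormal laboratory values at admission would cancel surgery; sections 4.5.2.4 and 4.5.7 only call for the tests and attach no such consequence.

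A subject whom the investigator withdraws for safety leaves under 4.6.3, and a new clock would not bring that subject back. This limits what the fix can recover. A 180-day value alone would also not yield the primary endpoint for someone never admitted, and postponed surgery needs its own rule, so a bare change of anchor would be incomplete. Section 5.1 counts the change from baseline, which might admit an enrollment value, but 4.1.1 and the Synopsis say admission, and the 180-day value is missing on either reading.

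What remains is that, followed as written, 4.5.2 and 5.10.1 leave a measurable primary outcome uncollected and then imputed.

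**Conclusion.** The point holds as a gap in the schedule. For a randomised subject who is never operated on, the protocol defines no follow-up visit and, before admission, no starting value for the primary endpoint, yet keeps the subject in the primary analysis. This conclusion rests on the text alone and on no assumed rate.

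Its size is uncertain and probably modest: 3-15 of 300 subjects under the assumed rates, and a bias anywhere from −0.14 to +0.14 mJOA points, zero included, under the assumptions above. It does not invalidate the trial. It should be changed because prevention is cheap and the data cannot be recovered later.

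**What to change.** Add to 4.5.2 and 5.10.1, in substance:

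- The rule covers a randomised subject who has not withdrawn consent and has not been operated on when the 180-day window opens, counted from the surgery date planned at randomisation (day 150 on that clock, as the window is ±30 days). For that subject the planned date serves as Day 0.
- The 180-day assessment is held on that clock.
- The baseline is the last pre-operative mJOA: admission if recorded, otherwise enrollment or screening.
- The observed change enters the ITT analysis. Imputation is used only if that visit is missed.
- A subject whose surgery is postponed but takes place before that window opens keeps the actual surgery date as Day 0.

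Subjects withdrawn by the investigator remain under 4.6.3. The change concerns measurement only and does not touch dosing or clinical care.

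**Cost:** a short paragraph, one already-defined clinic visit for a few subjects, and possibly a slightly less favourable ITT estimate.

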### 4.5.2.1 Pre-screening

---

Patients receiving care at the investigative sites will be pre-screened as potential subjects for the study. In order to do so, only the existing information obtained per standard routine medical procedures will be used. No study-specific screening procedures, activities or questionnaires will be performed during the pre-screening. Patients who fail pre-screening will not be recorded on any log or form.

### 4.5.2.2 Visit 1: Screening(15 or more days prior to surgery)

---

The first visit is the screening visit.

Patients considered potential candidates for the study based on pre-screening will sign an Internal Review Board (IRB)/Research Ethics Board (REB) approved informed consent form prior to participating in any study activities

- Obtain signed informed consent, place it in the patient file, make a copy and give it to the patient;
- Obtain signature on the HIPAA Authorization Form or equivalent Canadian health information release form;
- Assign a Subject Investigational Code (SIC);
- Verify that the patient meets all inclusion/exclusion criteria and perform the following:
  - Demographics
  - mJOA instrument (clinician administered) and calculation of the score
  - Clinical laboratory blood tests (liver function, creatinine, absolute neutrophils count). Test results obtained within 30 days before the screening are acceptable to this study
  - Pregnancy test (if applicable)
- Check Screening source worksheets for completeness
- Verify data and enter into eCRF within 14 calendar days of collection

### 4.5.2.3 Visit 2: Enrollment (15-21 days prior to surgery)

---

This visit occurs 15-21 days before the surgery and prior to the first dose of study medication. This visit can be performed on the same day as the screening visit or on two separate days. If performed on two separate days, the Investigator and the Study Coordinator should ensure that:

- The screening data are current

---

 Visit 1 and Visit 2 can be combined into one physical visit

Efficacy of Riluzole in Patients with Cervical Spondylotic Myelopathy Undergoing Surgical Treatment. A Randomized, Double-Blind, Placebo-Controlled, Multi-Center Study

- The patient's screening mJOA test was performed in less than 21 days prior to surgery. If not, repeat the mJOA.
- The patient's clinical manifestation has not significantly worsened (investigator's opinion) since the Visit 1. If yes, repeat the mJOA.

If the patient fails inclusion/exclusion criteria, the patient should not be enrolled to the study by the Investigator and the subject will be handled as a screen failure, the reason for the screen failure will be recorded on the screening source worksheet, data shall be entered into eCRF within 14 calendar days of data collection.

The following procedures are performed during the visit:

- Obtain socio-economic, health behavior, medical history, vitals, and information about concomitant medications
- Investigator:
  - Perform and record mJOA, Nurick Score, Grip Strength and complete ASIA examination
- Subject completes questionnaires:
  - NDI, Pain NRS, SF-36v2™, EQ-5D, Bazaz
- Review and verify all data collected to confirm the subject meets all study inclusion/exclusion criteria.
- **Enroll subject**
- Perform randomization procedure and enter randomization code into the Randomization Log
- Update information in the Screening Form
- Provide subject with *Bottle#1* of study medication and record on the Study Medication Dispensing CRF
- Provide subject with a Medication Compliance Diary to fill out the information about the treatment dates and times
- Teach subject how to take the medication and fill out the Medication Compliance Diary
- Inform subject to bring the Medication Compliance Diary and any unused medication with its container to the next visit (admission)
- Log the subject's drug accountability information into the Site Drug Accountability Log
- Advise subject not to take medications in the exclusion list
- Check source worksheets for completeness
- Verify data and enter into eCRF within 14 calendar days of collection

The first treatment dose should be administered in the morning of the 14th day before the surgery so that the surgery falls on the 15th day. For example, if the surgery is scheduled on Monday, the first dose of treatment medication will be administered on Monday morning two weeks before the surgery.

If the visit has occurred prior to the 14th day before the surgery, the site research coordinator will call the subject on the day -15 to ensure that the first dose of the medication will be administered as scheduled.

#### *4.5.2.4 Visit 3: Admission (pre-surgery)*

---

This visit occurs when the patient is admitted to the hospital for surgery. During the hospital stay the subject should receive scheduled study medication. Study coordinator should coordinate with the hospital pharmacy to assure that the subject receives the study medication during the hospital stay.

The following activities should be performed at admission:

- Record date and time of hospital admission
- Check and record AEs/SAEs
- Check and record concomitant therapy
- Obtain and record vital signs
- Obtain blood sample and order clinical lab tests
- Collect the medications and the Bottle #1 dispensed at enrollment visit.
- Count and record the remaining medication. The remaining medication and its container will be counted and compared with the data from Subject's Medication Compliance Diary. Record study medication compliance on the Medication Compliance CRF.
- Ensure the subject receives study medication during the hospital stay, and record in the Subject's Medication Compliance Diary. Bottle #2 should be dispensed on the surgery day (Day 0)
- Log the subject's drug accountability information into the Site Drug Accountability Log
- Investigator:
  - Obtain and record mJOA, Nurick, Grip Strength
  - Perform and record ASIA (complete)
- Subject:
  - Fill-out entire Subject pre-surgical source worksheet with data on health behavior, NDI, SF36v2.0, EQ-5D, Pain NRS, Bazaz
- Check source worksheets for completeness
- Verify data and enter into eCRF within 14 calendar days of collection

#### *4.5.2.5 Visit4: Procedure*

---

- Record operative data into source worksheets
- Obtain and record intra-operative and immediate postoperative AE/SAE
- Check source worksheets for completeness
- Verify data and enter into eCRF within 14 calendar days of collection

#### *4.5.2.6 Visit 5: Pre-discharge*

---

- Obtain and record vitals
- Obtain and record post-operative AE/SAEs
- Check and record concomitant therapy

#### Efficacy of Riluzole in Patients with Cervical Spondylotic Myelopathy Undergoing Surgical Treatment. A Randomized, Double-Blind, Placebo-Controlled, Multi-Center Study

- Provide subject with the remainder supply of study medication and record on the Medication Dispensing CRF
- Advise the subject the date when to stop taking trial medication (i.e. the 28th day after surgery is the last day to take the trial medication).
- Schedule appointment for the next visit (35 days after the date of surgery)
- Record time and date of hospital discharge
- Check source worksheets for completeness
- Verify data and enter into the eCRF within 14 calendar days of collection

##### *4.5.2.7 Visit 6: 35 days $\pm$ 5 days*

---

This is the first scheduled follow-up visit. The visit should occur at earliest 30 days from the date of surgery to allow subject to complete the 28 days of post-surgical treatment. The following activities should be performed during the visit.

- Subject returns bottle #2 with any remaining medication along with the Subject's Medication Compliance Diary. The remaining medication will be compared to the Subject's Medication Compliance Diary.
- Obtain and record concomitant therapy
- Obtain and record AE/SAE
- Obtain and record vitals
- Investigator performs and records:
  - ASIA (complete)
  - mJOA
  - Nurick
  - Grip Strength
- Obtain blood sample and order clinical lab tests
- Subject completes questionnaires for:
  - Health behavior
  - NDI
  - Pain NRS
  - EQ-5D
  - SF-36v2™
  - Bazaz
- Record study medication compliance in Medication Compliance CRF
- Log the subject's drug accountability information into the Site Drug Accountability Log
- Schedule next study visit (180 days post-surgery)
- Check Source Worksheets for completeness
- Verify data and enter into eCRF within 14 calendar days of collection

##### *4.5.2.8 Visit 7: 180 days $\pm$ 30 days*

---

This is the main endpoint study visit. The following activities should be performed during the visit.

- Obtain and record concomitant therapy
- Obtain and record AE/SAE

## Efficacy of Riluzole in Patients with Cervical Spondylotic Myelopathy Undergoing Surgical Treatment. A Randomized, Double-Blind, Placebo-Controlled, Multi-Center Study

- Investigator performs and records:
  - ASIA (complete)
  - mJOA
  - Nurick
  - Grip Strength
- Subject completes questionnaires for:
  - Health behavior
  - NDI
  - Pain NRS
  - EQ-5D
  - SF-36v2™
  - Bazaz
- Schedule next study visit (365 days post-surgery)
- Check Source Worksheets for completeness
- Verify data and enter into eCRF within 14 calendar days of collection

### *4.5.2.9 Visit 8: 365 days ±30 days*

---

The following activities should be performed during the visit.

- Obtain and record concomitant therapy
- Obtain and record AE/SAE
- Investigator performs and records:
  - ASIA (complete)
  - mJOA
  - Nurick
  - Grip Strength
- Subject completes questionnaires for:
  - Health behavior
  - NDI
  - Pain NRS
  - EQ-5D
  - SF-36v2™
  - Bazaz
- Check Source Worksheets for completeness
- Verify data and enter into eCRF within 14 calendar days of collection

### *4.5.2.10 Unscheduled Visit*

---

- Obtain and record concomitant therapy
- Obtain and record AE/SAE
- Check Source Worksheets for completeness
- Verify data and enter into eCRF within 14 calendar days of collection

### 4.5.3 Enrollment and Randomization

---

Patient enrollment occurs at the time of randomization. If a patient is consented, screened, and, for any reason, does not get randomized, the patient will not be considered enrolled into the study.

Patient randomization occurs at Visit 2 (Enrollment), 15-21 days prior to the surgery. The randomization will occur by opening the lowest sequential number of the sealed randomization envelopes. Inside the envelope there will be a unique patient randomization number. The study coordinator will match the unique patient randomization number with the number on the medication container. The randomization will be recorded in the Randomization Log.

### 4.5.4 Study Drug Procedures

---

#### 4.5.4.1 Dispensing the study drug

---

Each study site will be supplied with the study drug. All study drug containers will have identical appearance. Each container will be labeled with a unique number that will match the number in the randomization envelope. Bottle#1 will contain 17-day supply (i.e. 34 capsules) of the study medication and Bottle#2 will contain 31-days supply (i.e. 62 capsules).

Authorized site research staff will select the study drug package to dispense to the subject by matching the container label to the unique randomization number identified in the randomization envelope. Randomization will be recorded in the Randomization Log.

Study Subjects will be instructed:

- To take one capsule every 12 hours.
- Study medication should be taken at least one hour before, or 2 hours after a meal to avoid food-related decrease in bioavailability.
- If a dose is missed, take the next capsule as originally planned.
- To store the study drug at the temperature between 20°-25°C (68°-77°F) protected from bright light.

#### 4.5.4.2 Breaking the Randomization Code

---

The CRO will be responsible for randomization assignment and will hold a key to un-blind the case assignment in case of emergency. In the event of an emergency the principal investigator at the site will make the decision about the un-blinding of the case. The reason for un-blinding will be recorded and submitted to IRB\REB and Sponsor/CRO.

